# Enteral Nutrition Tolerance And REspiratory Support (ENTARES) Study in preterm infants: study protocol for a randomized controlled trial

**DOI:** 10.1186/s13063-018-3119-0

**Published:** 2019-01-18

**Keywords:** Feeding intolerance, RDS, HFNC, NCPAP, Preterm, NEC, Enteral nutrition, Non-invasive ventilation, Very low birth weight infant

## Abstract

**Background:**

Respiratory distress syndrome (RDS) and feeding intolerance are common conditions in preterm infants and among the major causes of neonatal mortality and morbidity.

For many years, preterm infants with RDS have been treated with mechanical ventilation, increasing risks of acute lung injury and bronchopulmonary dysplasia.

In recent years non-invasive ventilation techniques have been developed. Showing similar efficacy and risk of bronchopulmonary dysplasia, nasal continuous positive airway pressure (NCPAP) and heated humidified high-flow nasal cannula (HHHFNC) have become the most widespread techniques in neonatal intensive care units. However, their impact on nutrition, particularly on feeding tolerance and risk of complications, is still unknown in preterm infants.

The aim of the study is to evaluate the impact of NCPAP vs HHHFNC on enteral feeding and to identify the most suitable technique for preterm infants with RDS.

**Methods:**

A multicenter randomized single-blind controlled trial was designed. All preterm infants with a gestational age of 25–29 weeks treated with NCPAP or HHHFNC for RDS and demonstrating stability for at least 48 h along with the compliance with inclusion criteria (age less than 7 days, need for non-invasive respiratory support, suitability to start enteral feeding) will be enrolled in the study and randomized to the NCPAP or HHHFNC arm. All patients will be monitored until discharge, and data will be analyzed according to an intention-to-treat model.

The primary outcome is the time to reach full enteral feeding, while parameters of respiratory support, feeding tolerance, and overall health status will be evaluated as secondary outcomes. The sample size was calculated at 141 patients per arm.

**Discussion:**

The identification of the most suitable technique (NCPAP vs HHHFNC) for preterm infants with feeding intolerance could reduce gastrointestinal complications, improve growth, and reduce hospital length of stay, thus improving clinical outcomes and reducing health costs. The evaluation of the timing of oral feeding could be useful in understanding the influence that these techniques could have on the development of sucking-swallow coordination. Moreover, the evaluation of the response to NCPAP and HHHFNC could clarify their efficacy as a treatment for RDS in extremely preterm infants.

**Trial registration:**

ClinicalTrials.gov, NCT03548324. Registered on 7 June 2018.

**Electronic supplementary material:**

The online version of this article (10.1186/s13063-018-3119-0) contains supplementary material, which is available to authorized users.

## Background

Respiratory distress syndrome (RDS) is a common condition in premature infants and one of the major causes of neonatal mortality [1]. For many years, preterm infants with RDS have been treated with mechanical ventilation, increasing the risks of acute lung injury and long-term morbidity, such as bronchopulmonary dysplasia (BPD) [2–5]. Offering an appropriate respiratory support in the delivery room, together with early surfactant administration, can allow one to avoid or limit endotracheal ventilation with better outcomes in terms of mortality and short- and long-term complications, above all BPD [6]. Early nasal continuous positive airway pressure (NCPAP) treatment combined with surfactant replacement therapy decreases the need for mechanical ventilation and has been recommended as the first line treatment for RDS [7, 8]. However, NCPAP has significant limitations, mainly related to the type of interface needed. Excessive leaks around the prongs or mask and through the mouth can lead to inadequate support, whereas excessive pressure may result in pneumothorax and damage to the nose and face. Moreover, the bulky fixation devices obscure the infant’s face, interfering with both feeding and positioning [9]. In recent years, heated humidified high-flow nasal cannula (HHHFNC) has been studied as an alternative non-invasive respiratory support (NRS). HHHFNC became popular partially due to some perceived advantages related to the type of interface used. Cannulas are easier to apply than NCPAP prongs or mask, may be more comfortable for infants, and may enable easier access to babies’ faces, thus facilitating feeding and parental bonding [10–12]. Whereas the practical advantages seem to be established, there is controversy about HHHFNC efficacy as respiratory support [13–15]. Recent studies support that HHHFNC is as effective as NCPAP for the primary treatment of RDS, but evidences are still insufficient and data are still lacking, especially for the extremely preterm population (< 28 weeks’ gestation) [14, 16–18]. A recent Cochrane review comparing HHHFNC with other NRS measures showed equivalent rates of treatment failure and similar rates of BPD when used as a post-extubation support in preterm infants [19]. With equivalent effectiveness, the choice of the most adequate NRS should consider the impact on the health status of the premature infant, evaluating above all the effect on nutrition and growth. Along with RDS, feeding intolerance (FI) represents a relevant issue in preterm infants, and the coexistence of the two represents a great challenge for the neonatologist [20]. Because of gastrointestinal immaturity, a considerable proportion of premature infants will develop clinical symptoms of FI, causing interruptions of feeding. This delays the establishment of adequate enteral nutrition and prolongs the need for parenteral nutrition, thus increasing the risk of infections and prolonging hospital stay [21]. Avoiding FI and its complications, such as necrotizing enterocolitis (NEC), is a priority for the neonatologist, who often faces the challenge of interpreting the clinical and prognostic significance of common and aspecific signs of FI. Clear identification of the parameters that should be evaluated to identify FI is still lacking in the literature, although, among controversy, the presence of gastric residuals, vomits and/or regurgitations, and abdominal distension and the onset of crises of apnea/bradycardia are considered the most frequent signs [22, 23]. A correlation between non-invasive ventilation and the occurrence of FI and NEC is plausible, although the mechanisms through which ventilation may induce FI and its incidence in ventilated infants are still unclear [20, 24]. The most common hypothesis is that pressurized gases that are not completely conveyed to the airways could cause bowel distension. Bowel distension in infants on CPAP was described by Jaile et al. [25] as *CPAP belly syndrome*, but no inferences about feeding tolerance and risk of NEC were drawn. More recent studies evaluated the effect of CPAP on mesenteric flow and gastric emptying, suggesting a role of CPAP as a risk factor for FI [26–28]. No specific studies have been designed to evaluate the impact of different types of NRS on FI and the occurrence of NEC, which are generally evaluated as secondary outcomes, susceptible to data analysis and patient selection biases. Our hypothesis is that different techniques of NRS may have different impacts on feeding issues in preterm infants.

We therefore intend to compare the application of NCPAP and HHHFNC in preterm infants with RDS to evaluate their impact on FI.

## Methods

### Aims

The aims of the study are to evaluate the effects of different NRS techniques (NCPAP vs HHHFNC) on feeding tolerance in preterm infants with RDS and to evaluate their impact on full enteral feeding (FEF) achievement and acquisition of oral feeding. A further aim is to evaluate the response to NCPAP and HHHFNC as treatment for RDS in extremely preterm infants.

### Study design and setting

The study has been designed as a multicenter randomized no-mask controlled trial. It will involve the major Italian neonatal intensive care units (NICUs) and will be coordinated by the NICU of the University of Turin.

### Inclusion criteria

All infants admitted to the NICUs with a gestational age between 25 and 29 weeks and who will have met the following inclusion criteria will be consecutively enrolled in the study:Presence of RDSPeriod of stability on HHHFNC or NCPAP for at least 48 h in the first 5 days of life (SatO_2 TC_ 90–95%, pCO_2_ ≤ 60 mmHg, FiO_2_ < 40%, Silverman score [29] ≤ 6, ≤ 2 apnea episodes/h with CPAP ≤7 cmH_2_O if on NCPAP, and flow ≤7 L/min if on HHHFNC)≤ 7 days of lifeSuitability to start enteral feeding (if already started it should be less than 75 mL/Kg/day)Parental written consent

### Exclusion criteria

The following are the study exclusion criteria:Neurological or surgical diseasesSepsisChromosomal abnormalitiesMajor malformations

### Recruitment and randomization

Informed written consent will be signed by both parents, and sufficient time will be allowed for consent. Non-Italian-speaking parents will only be asked for their consent if an adult interpreter is available. Trust interpreter and link worker services will be used to support involvement of participants whose first language is not Italian.

Eligible patients will be allocated to one of the two arms (NCPAP or HHHFNC) by block randomization. A software has been designed to automatically generate a randomization code and to obtain, in each research unit, a balance between patients with gestational age < 28 weeks and ≥ 28 weeks in both arms. The randomization software will be available for all research units, on a password-protected platform on the Enteral Nutrition Tolerance And REspiratory Support (ENTARES) website, and will generate a randomization sequence to which all clinicians are blind.

### Monitoring and data collection

Each research unit will adopt its own protocols for clinical management of the patients enrolled in the study while still respecting some minimal standard criteria for respiratory support and enteral nutrition, common for all participating units and defined as follows.

#### Minimal standard criteria for respiratory support

The suggested initial setup is [30, 31]:CPAP between 5 and 7 cmH_2_O if on NCPAP and flow between 4 and 7 L/min if on HHHFNCFiO_2_ set to reach pO_2_ = 50–60 mmHg (capillary/arterial blood gas test) and SatO_2_ TC = 90–95%

The criteria to try weaning are [30, 31]:CPAP < 4 cmH_2_O if on NCPAP and flow < 2 L/min if on HHHFNCFiO_2_ < 25% to maintain pO_2_ = 50–60 mmHg (capillary/arterial blood gas test) and SatO_2 TC_ = 90–95%

The failure criteria are [30, 31]:FiO_2_ > 40%pH < 7.2pCO_2_ > 65 mmHg≥ 3 episodes of desaturations (SatO_2 TC_ ≤ 80%) per hour≥ 3 episodes of apnea (> 20 s) and/or bradycardia (FC ≤ 80 beats per minute (bpm)) per hourSilverman score [29] > 6

#### Minimal standard criteria for enteral nutrition

The decision to increase volume of feeds will be up to the clinicians and in accordance with the protocol used in their own NICU; however, a maximum cut-off for feeding progression was set at 30 mL/kg/day [32, 33].

The indications for the interruption of feeding are based on abdominal examination, the occurrence of vomits/regurgitations and cardiorespiratory events, and the evaluation of alvus and gastric residual volumes (evaluated if required by the protocol in use) as detailed in Table 1 [22, 34, 35]. A score system was developed to evaluate abdominal distension (Table 2).

**Table 1 Tab1:** Criteria for the interruption of enteral feeding

	Minor criteria	Major criteria
Physical examination	• Abdominal distension • Visible bowel ansa • Abdominal distension responsive to gastric suction/rectal stimulation	• Dyschromic abdominal wall • Abdominal distension not responsive to gastric detension/rectal stimulation • Painful abdomen
Regurgitations/vomits	• ≤ 2 episodes between 2 feeds or in the previous 3 h (if not fed)	• > 2 episodes between 2 feeds or in the previous 3 h (if not fed) • Bilious vomiting/hematemesis
Gastric residual volumes (GRVs)^a^	• GRV < 100% of previous feed (bilious or with hematic fragments)	• Hematic/fecaloidal GRV • GRV ≥ 100% of previous feed
Alvus	• Mucous stools	• Hematic stools
Cardiorespiratory (CR) events	• ≥ 3 CR events^b^/h	• ≥ 1 extreme CR event^c^
0–1 minor criteria:	- Continue enteral feeding with increments as per protocol (max 30 mL/kg/day)	
2 minor criteria:	- Stop increasing feeds, re-assess prior to the next feed, and evaluate GRV if not done before - If 2 minor criteria in at least 2 consecutive evaluations, consider reducing volume of feed	
1 major criterion or 3 minor criteria:	- Interrupt enteral feeding and re-assess prior to the next feed	

^a^The evaluation of GRVs is elective and according to the protocol of each research unit. GRVs are considered pathological according to minor and major criteria

^b^CR events were defined as episodes of apnea lasting more than 20 s or more than 5 s if followed by desaturation or bradycardia, episodes of desaturation with blood oxygen saturation below 80%, and episodes of bradycardia with heart rate below 80 beats per minute

^c^Extreme CR events were defined as CR events requiring resuscitation

**Table 2 Tab2:** Abdominal distension score

Extent of distension	Score
Abdomen is not distended	0
Abdomen is distended but not tense	1
Abdomen is distended and tense, responsive to gastric suction/rectal stimulation	2
Abdomen is distended and tense, not responsive to gastric detension/rectal stimulation	3

Data on respiratory support, nutrition, growth, and overall clinical status will be collected from enrollment to discharge. According to an intention-to-treat model, each patient will be monitored whatever the occurring clinical events, including the failure of the modality of respiratory support assigned at enrollment. Death or transfer to another hospital before reaching FEF will be the only reasons for a patient to drop the study.

All data to be collected will be obtained from the clinical records. Data will be recorded on a common database available on the ENTARES website and specifically designed for this study. Access to the database will be password protected, and data will be entered by the local principal investigator. Participants will be identified by trial number only.

All data recorded throughout the study period are listed in Table 3.

**Table 3 Tab3:** Data recorded during the study period

Ventilation/respiration parameters^a^	
– Respiratory support technique – PEEP/CPAP (cmH_2_O) – Peak inspiratory pressure (PIP, cmH_2_O) – Flow (L/min) – FiO_2_ (%) – Respiratory rate (acts/min) – Transcutaneous O_2_ blood saturation (SatO_2 TC_ %) – Capillary/arterial blood gas test – Episodes of apnea (> 20 s or > 5 s if followed by bradycardia/desaturation), bradycardia (Heart rate ≤ 80 bpm) and desaturation (SatO_2 TC_ ≤ 80%)/day – Silverman score	
Feeding parameters^b^	
– Parenteral nutrition intake (mL/kg/day) – Enteral nutrition intake (mL/kg/day) – Total caloric intake (Kcal/kg/day) – Type of milk: human milk or formula – Modality of feeding (bolus, gavage, continuous feeding) – Modality of fortification (if any; type of fortifier: standard, target, or adjustable fortification) – Enteral feeding interruptions (episodes/day) – Not given feeds (episodes/day) – Pathologic gastric residual volumes (episodes/day) – Vomits and/or regurgitations (episodes/day) – Abdominal distention (medium score/day)	
Auxological parameters^c^	
– Weight (g) – Length (cm) – Cranial circumference (cm)	
Overall health status parameters^d^	
– Patent ductus arteriosus – Intraventricular hemorrhage – Leukomalacia – Retinopathy of prematurity – Pneumothorax – Blood transfusion – NEC – Intestinal perforation	

^a^Ventilation/respiration parameters will be recorded at enrollment, at achievement of half enteral feeding and full enteral feeding, at the beginning of oral feeding, at achievement of full oral feeding, and at any change in respiratory assistance strategy. Apnea monitoring will extend until any respiratory support is needed (except for O_2_ supplementation per nasal cannula)

^b^Feeding parameters will be recorded daily until full enteral feeding is achieved, at the beginning of oral feeding, at achievement of full oral feeding, and at any change in respiratory assistance strategy

^c^Auxological parameters will be recorded at the time of enrollment, upon achieving half enteral feeding and full enteral feeding, and at discharge

^d^Relevant clinical events/diagnosis will be recorded from enrollment until discharge

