### Outcomes

The primary outcome of the study is the time needed to reach FEF, defined as an enteral intake of 150 mL/Kg/day. Secondary outcomes are listed in Table 4.

**Table 4 Tab4:** Secondary outcomes

– Time to reach HEF, defined as an enteral intake of 75 mL/Kg/day (days) – Interruptions of enteral feeding (episodes/day) – Not given feeds (episodes/day) – Pathologic gastric residual volumes (episodes/day) – Vomits and/or regurgitations (episodes/day) – Abdominal distention (mean score/day) – Beginning of oral feeding (post-menstrual age) – Time to reach full oral feeding (number of days) – Post-menstrual age at full oral feeding (weeks) – Weight growth (∆ z-score) – Duration of the respiratory support assigned at randomization (days) – Total duration of respiratory support need (days) – Failure of the respiratory support assigned at randomization (yes/no) – Length of hospital stay (days) – Duration of central venous catheter (days) – Clinical events and complications (NEC, bowel perforation, pneumothorax, BPD, PDA, ROP, IVH, PVL) – Transfers to other hospitals or deaths before reaching full enteral feeding (number of patients)	

*HEF* half enteral feeding, *NEC* necrotizing enterocolitis, *BPD* bronchopulmonary dysplasia, *PDA* patent ductus arteriosus, *ROP* retinopathy of prematurity, *IVH* intraventricular hemorrhage, *PVL* periventricular leukomalacia

The design of the study is outlined in Fig. 1. The Standard Protocol Items: Recommendations for Interventional Trials (SPIRIT) figure of enrollment, interventions, and assessments is shown in Fig. 2. The SPIRIT checklist is provided as Additional file 1.

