### Statistical analysis and sample size

Time to reach FEF, the primary outcome, will be analyzed by Kaplan and Meier survival analysis according to the intention-to-treat principle. The two arms will be compared with the log-rank Test [36].

Regarding secondary outcomes, the time to reach half enteral feeding and time to reach full oral feeding will be estimated by Kaplan and Meier analysis, the failure of the respiratory support assigned at randomization will be compared using Fischer’s exact test, and the other secondary outcomes will be estimated using appropriate generalized linear models. This will be a single-blind trial where the blinded person will be the statistician.

Based on a population of infants with a gestational age < 30 weeks who are consecutively admitted to the NICUs of each research unit from January to June 2017 (mean time of FEF 19.6 days) and considering a ratio between the subjects of the two arms of 1:1, a sample size of at least 141 patients per arm has been calculated to observe a difference of 30% between the two arms (5.7 days).

An interim analysis is planned upon reaching the enrollment of half of the patients expected by the sample size calculation.

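### Time to full enteral feeding is analysed by Kaplan-Meier and log-rank with no rule for death as a competing event, so infants who die or are transferred first are by default censored

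*Protocol article*

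**What the plan says.** In the Outcomes section: "The primary outcome of the study is the time needed to reach FEF, defined as an enteral intake of 150 mL/Kg/day". Death is not part of this outcome.

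The section on statistical analysis and sample size fixes the method: "Time to reach FEF, the primary outcome, will be analyzed by Kaplan and Meier survival analysis according to the intention-to-treat principle". For the test it adds: "The two arms will be compared with the log-rank Test". Time to half enteral feeding and time to full oral feeding are also to be estimated by Kaplan-Meier.

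In the text after Table 2, under the criteria for enteral nutrition, infants are to be followed whatever happens clinically, and then comes the exception: "Death or transfer to another hospital before reaching FEF will be the only reasons for a patient to drop the study".

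Deaths and transfers before FEF are used in one other place, as a single entry among the secondary outcomes in Table 4: "Transfers to other hospitals or deaths before reaching full enteral feeding (number of patients".

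The article does not use the word censored. It mentions no competing risk, no cumulative incidence and no composite with death.

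**The concern.** The exit rule, the estimator and the test are all fixed, and nothing is said about infants who leave without the event. In a Kaplan-Meier and log-rank analysis such infants are censored at exit unless the plan says otherwise. Censoring treats them as if they could still reach FEF later, at the same rate as those still being fed.

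For a dead infant that is false. Death may also lie on the pathway under study. The Abstract names respiratory distress syndrome and feeding intolerance among the main causes of neonatal death and illness, and the Background calls a link between non-invasive ventilation, feeding intolerance and necrotizing enterocolitis plausible. Equal deaths by arm, unrelated to feeding, therefore cannot be taken for granted.

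Transfer is a different and weaker problem. A transferred infant can still reach FEF, so a primary outcome that could be obtained is lost, although the analysis is described as intention to treat. Transfer may also depend on clinical state, which would make the censoring informative.

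At stake is whether the primary curves and test describe all randomised infants or only the rate of reaching FEF among those still alive and in the study.

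**Working it through.** The article gives no figure on this point to reproduce.

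**Inputs from the article** (Statistical analysis and sample size): mean time to FEF 19.6 days; 141 infants per arm.

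**Assumed, because the article is silent:** the shape of the FEF-time distribution, and the proportion q dying before FEF.

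**Step 1. What the Kaplan-Meier curve shows.** Take FEF times as Weibull with shape 1.5. Scale = 19.6 / Γ(1 + 1/1.5) = 19.6 / 0.9027 = 21.71 days. With deaths censored and independent of feeding, 1-KM(t) = 1 − exp[−(t/21.71)^1.5]. At day 60 this is 1 − exp(−4.594) = 99.0%, whatever the death rate.

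**Step 2. What share of randomised infants reaches FEF.** With a constant death hazard m, chosen so that a proportion q dies before FEF, cumulative incidence is CIF(t) = ∫₀ᵗ f(u)·exp(−mu) du, where f is the Weibull density.

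| q | m per day | CIF day 30 (1-KM 80.3%) | CIF day 60 (1-KM 99.0%) | Median days (KM 17.0) |
|---|---|---|---|---|
| 3% | 0.00157 | 78.5% | 96.1% | 17.2 |
| 6% | 0.00320 | 76.7% | 93.2% | 17.5 |
| 10% | 0.00551 | 74.2% | 89.3% | 17.9 |

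The gap is wide late in the curve (3 to 10 points at day 60) and narrow at the median (under 1 day).

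**Step 3. Does the shape matter?** With exponential times of mean 19.6 days, λ = 1/19.6 = 0.0510, m = λq/(1 − q) and CIF(t) = (1 − q)(1 − exp[−(λ + m)t]). At q = 10%, day 60: 0.90 × (1 − exp(−0.05669 × 60)) = 0.90 × 0.967 = 87.0%, against 1-KM = 1 − exp(−60/19.6) = 95.3%. At q = 5% and 15% the CIF is 91.2% and 82.7%. The pattern is the same.

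**Step 4. What the test sees.** Simulation with 141 per arm, the Weibull model of Step 1 in both arms, deaths independent of feeding, two-sided 5% level, 6,000 runs. A negative z means that the arm with more deaths looks slower.

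| Deaths by arm | Deaths censored: mean z, rejections | Dead kept as never reaching FEF: mean z, rejections |
|---|---|---|
| 6% vs 6% | 0.0, 5.3% | 0.0, 5.4% |
| 10% vs 10% | 0.0, 5.1% | 0.0, 5.0% |
| 3% vs 5% | 0.0, 4.8% | −0.5, 7.6% |
| 3% vs 10% | 0.0, 5.0% | −1.5, 32.2% |

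The censored log-rank keeps its level and does not register the deaths. The two analyses diverge clearly only when deaths are unbalanced.

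**Step 5. Stress case: deaths related to feeding.** Gamma times (shape 2, mean 19.6 days) in both arms, the slowest feeders die, 5% vs 15%, 4,000 runs. The censored log-rank has mean z +0.72, in favour of the arm with more deaths, and rejects in that direction in 11.3% of runs (nominal 2.5%). Keeping the dead as never reaching FEF gives mean z −1.07. This split and this mechanism are deliberately extreme.

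**The case against.** **Censoring is an inference.** The article says only that these infants leave the study. A full protocol or analysis plan, not shown here, could keep deaths at risk as not having reached FEF, and the same test would accommodate that. This stands, which is why the point is about the default and the absence of a rule, not about a stated rule.

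**The log-rank is not invalid.** A reader might infer that the primary test is wrong. Step 4 does not support that: with equal feeding speed and deaths unrelated to feeding, it rejects at the nominal 5%. Gray's test answers a different question and would reject in about a third of runs at 3% vs 10% deaths with identical feeding speed. Which should be primary is a choice of estimand.

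**The size rests on assumptions.** Infants enter only after 48 hours of respiratory stability, and sepsis, surgical or neurological disease and major malformations are excluded, so pre-FEF deaths may be few. A 3% vs 10% split would dominate the trial's interpretation in any case. Day 60 shows the gap at its most visible; the medians hardly move. All of this stands.

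**Deaths are not hidden.** They appear in Table 4, though pooled with transfers, so an imbalance in deaths could be blurred by transfers.

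**The Abstract's sentence is not a separate error.** "All patients will be monitored until discharge, and data will be analyzed according to an intention-to-treat model" could be read as contradicting the exit rule. It is a summary, and the Methods give the exception. What remains is the loss of outcome data after transfer.

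**Durations in the secondary outcomes.** A reader might also infer that early death would count as a short, favourable hospital stay or support time. The article says only that "the other secondary outcomes will be estimated using appropriate generalized linear models". Nothing states that a stay cut short by death is entered as complete, so no claim is made on this.

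**Conclusion.** The point holds in a limited form. As written, the plan has no competing-event rule for its primary outcome, and its default is to censor infants who die or are transferred before FEF. Since death rules out FEF, 1-KM overstates the proportion of randomised infants reaching it: by about 3, 6 and 10 percentage points at day 60 if 3%, 6% and 10% die first, under the Weibull assumption. An arm with more deaths is not penalised. The bias is small if deaths are few and balanced, and the article gives no rate.

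The log-rank with deaths censored remains a valid cause-specific comparison if deaths are unrelated to feeding progress. It does not describe time to FEF in all randomised infants, which is how an intention-to-treat analysis will be read. Should-fix.

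**What to change.** - Replace the Kaplan-Meier curves for FEF with cumulative incidence by arm, with death as a competing event.
- Report a test that keeps dead infants at risk as never reaching FEF (Gray's test) together with the cause-specific log-rank, and state in advance which is primary.
- Apply the same to half enteral feeding and full oral feeding.
- Report deaths and transfers before FEF as separate counts by arm.
- Keep transferred infants in the study: request the FEF date from the receiving hospital, and censor at transfer only if it cannot be had.

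The cost is some additional analysis and one date per transferred infant, which is best sought while the trial is running. If Gray's test is made primary, the estimand becomes time to FEF with death counted as not reaching it, and the plan should say so.

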### Safety

Safety endpoints will include incidence, severity, and causality of reported significant adverse events (SAEs). All SAEs will be followed until satisfactory resolution or until the investigator responsible for the care of the participant deems the event to be chronic or the patient to be stable. All expected and unexpected SAEs, whether or not they are attributable to the study intervention, will be reviewed by the local principal investigators to determine if there is a reasonable suspected causal relationship with the intervention. If the relationship is reasonable, SAEs will be reported to the chief investigators, who will then report them to the ethics committee and inform all other investigators to guarantee the safety of the participants.

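### The rule that an infant transferred before full enteral feeding leaves the study conflicts with the stated follow-up to discharge and gives complications arising after the move no stated route into the comparison of arms

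*Protocol article*

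**What the plan says.** The rule stands in the text after Table 2, in the part of the Methods on monitoring and data collection: "Death or transfer to another hospital before reaching FEF will be the only reasons for a patient to drop the study".

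Other statements in the same article set a longer follow-up:

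- Abstract, Methods: "All patients will be monitored until discharge, and data will be analyzed according to an intention-to-treat model".
- The same paragraph as the rule: "Data on respiratory support, nutrition, growth, and overall clinical status will be collected from enrollment to discharge", and, under intention-to-treat, "each patient will be monitored whatever the occurring clinical events".
- Table 3, footnote d: "Relevant clinical events/diagnosis will be recorded from enrollment until discharge".
- Safety section: "All SAEs will be followed until satisfactory resolution or until the investigator responsible for the care of the participant deems the event" chronic or the patient stable. No exception is made for transfer.

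Table 4 lists the complications among the secondary outcomes: "Clinical events and complications (NEC, bowel perforation, pneumothorax, BPD, PDA, ROP, IVH, PVL"). It also counts departures: "Transfers to other hospitals or deaths before reaching full enteral feeding (number of patients"). Data come from clinical records and are entered by the local principal investigator.

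**The concern.** Table 4 makes complications such as necrotising enterocolitis (NEC), bronchopulmonary dysplasia (BPD), retinopathy (ROP) and periventricular leukomalacia (PVL) secondary outcomes of a randomised comparison. Some can appear well after enrolment. If an infant leaves the study on transfer before FEF, any such event that starts or is confirmed after the move goes unrecorded, although the article promises recording to discharge.

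The loss is also tied to the primary outcome. An infant who has reached FEF and is then moved is not dropped; one who has not reached it is. Retention for the complication outcomes therefore depends on a post-randomisation event that the treatments are expected to change. The groups with complete complication data may then no longer be the groups as randomised, which is what the stated intention-to-treat model is meant to protect.

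This point concerns the complication and safety outcomes. It does not concern how time to FEF is censored.

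**Working it through.** **1. Apply the statements to four infants.**

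- *Complication diagnosed before the move.* Footnote d records events from enrolment, so it is captured. No loss.
- *SAE still open at a move before FEF.* The Safety section keeps it under follow-up; the rule says the infant has left. The two conflict.
- *Complication first arising or confirmed after a move before FEF.* The Abstract, the data-collection paragraph and footnote d say it is recorded; the rule says the infant has left. The statements conflict, and no route from the receiving hospital is given.
- *Same complication after a move that follows FEF.* The rule does not apply, so the infant stays in and the event counts.

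The third and fourth infants differ only in whether FEF had been reached.

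**2. Exposure to the rule by arm.** Inputs from Statistical analysis and sample size: mean time to FEF 19.6 days, target difference 5.7 days, 1:1 allocation, 141 infants per arm.

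The target difference is described as 30%. In fact 0.30 × 19.6 = 5.88 days, and 5.7 / 19.6 = 29.1%. The discrepancy hardly matters here:

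- With 5.7 days: 19.6 − 5.7 = 13.9, and 19.6 / 13.9 = 1.41.
- With 5.88 days: 19.6 − 5.88 = 13.72, and 19.6 / 13.72 = 1.43.

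With the same small daily chance of transfer *h* in both arms, the expected number dropped per arm is about 141 × *h* × mean days to FEF. The ratio between arms is then the ratio of mean times, about 1.4. No assumption about why infants are transferred is needed.

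The ratio does assume that 19.6 days is the slower arm's mean and that the days run from entry to the study. The alternatives are:

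- 19.6 days as the faster arm's mean: (19.6 + 5.7) / 19.6 = 25.3 / 19.6 = 1.29.
- Days counted from birth, with entry on day 7 (the latest age allowed): (19.6 − 7) / (13.9 − 7) = 12.6 / 6.9 = 1.83.

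**3. Illustration with an assumed transfer rate.** The article gives none. Suppose 5% to 10% of the 2 × 141 = 282 infants move before FEF:

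- 282 × 0.05 = 14.1 and 282 × 0.10 = 28.2 infants.
- Slower arm's share: 19.6 / (19.6 + 13.9) = 0.585.
- At 5%: 14.1 × 0.585 = 8.2 in the slower arm and 5.9 in the faster.
- At 10%: 28.2 × 0.585 = 16.5 and 11.7.

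These are infants with incomplete follow-up for complications, not missed events. How many events are missed depends on event rates after transfer, which the article does not give.

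**The case against.** **The paragraph can be read as a rule followed by its exception.** It promises follow-up to discharge and then names the only ways out; and discharge is not defined as final discharge home. This has some force for that paragraph. It does not reconcile the Abstract, which speaks of all patients, or footnote d and the Safety section, which carry no exception. Even where the exception reading is accepted, retention still depends on reaching FEF.

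**The full protocol may describe retrieval of data from receiving hospitals, and missing-data handling belongs in the analysis plan.** This is right, and the lack of such detail in an article is not the point. The point is a stated rule that contradicts other stated rules.

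**Departures are visible.** Table 4 counts transfers and deaths before FEF, so an imbalance would show. That stands, but the count tells how many left, not what happened to them.

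**Stronger readings that the documents do not support:**

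- *Safety follow-up stops at transfer.* The Safety section follows SAEs to resolution, chronicity or stability with no transfer exception.
- *The NEC or perforation that prompts a transfer is lost.* A diagnosis that leads to a move precedes it and falls within the recording window of footnote d. No passage says why infants are transferred.
- *A true excess of gut complications in one arm would be shrunk.* One might calculate that a true 10% versus 5% (5 points) appears as 5 × 0.75 = 3.75 or 5 × 0.5 = 2.5 points if 25% or 50% of events go unrecorded. Every input is assumed, and dropped infants are taken as event-free, which the article does not state. The proportional loss is also equal in both arms, so the risk ratio stays at 2.0 and no preferential loss is shown. The inputs are strained as well: 141 × 10% = 14.1 events, of which half is 7, while 5% transfers from 141 is also about 7 infants, so every transferred infant would need an unrecorded event.

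**Conclusion.** The point holds as a contradiction with a limited consequence. The rule on leaving the study cannot be squared with monitoring of all infants to discharge, recording of clinical events to discharge and SAE follow-up to resolution. What is exposed is confined to Table 4 complications that first arise or are confirmed after a transfer before FEF, for example later NEC, BPD, ROP or PVL, together with the unclear status of SAEs open at the move.

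The loss can differ by arm because it depends on the primary outcome. Exposure is about 1.4 times as long in the slower arm under the target effect, given an equal and small daily chance of transfer; the alternative readings in the check give 1.29 to 1.83. If the arms reach FEF at the same speed, this mechanism gives no imbalance.

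The direction and size of any bias in the complication rates cannot be derived from the documents. Severity is low to moderate: the primary analysis is outside this point, and only secondary and safety outcomes are touched.

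**What to change.** Reconcile the Abstract, the data-collection paragraph, footnote d of Table 3 and the Safety section by stating that:

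- transfer before FEF ends only the daily feeding and respiratory records;
- Table 4 clinical events and SAEs are still collected to final discharge, either from the receiving hospital's discharge summary, entered by the enrolling unit's investigator, or directly by the receiving unit if it takes part in the trial;
- these events are analysed in all randomised infants;
- the number of infants whose status after transfer is unknown is reported by arm, beside the count of transfers and deaths already in Table 4.

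This changes data collection and not clinical care. It costs a short wording amendment and one discharge summary per transferred infant, requested by existing staff. The downside is a small record-retrieval burden and some summaries that cannot be obtained; reporting the unknowns by arm makes that remainder visible.
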